### ***7.2.2. Treatment-Emergent Hypertension***

The dose modification schedule for treatment-emergent hypertension during study drug dosing should be followed. Participants' Blood Pressure (BP) measurements will be monitored and appropriate treatment to effectively control hypertension is required.

(Table on next page).

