| Grade 2               | Systolic BP 140-159 mmHg or diastolic BP 90-99 mmHg
OR
Symptomatic increase by > 20 mmHg (diastolic) if previously within normal limits                            | Treat with the aim to achieve diastolic BP $\leq$ 90 mmHg
- If BP previously within normal limits, start anti-hypertensive monotherapy
- If participant already on anti-hypertensive medication, titrate up the dose. | Continue regorafenib.
If symptomatic, hold regorafenib until symptoms resolve AND diastolic BP $\leq$ 90 mmHg a .
When regorafenib is restarted, continue at the same dose level                                                                                                                                                                                                                                  |
| Grade 3               | Systolic BP $\geq$ 160 mmHg or diastolic BP $\geq$ 100 mmHg
OR
More than one anti-hypertensive medication or more intensive therapy than previously used indicated | Treat with the aim to achieve diastolic BP $\leq$ 90 mmHg
- Start anti-hypertensive medication
AND/OR
- Increase current anti-hypertensive medication
AND/OR
- Add additional anti-hypertensive medications. | Hold regorafenib until diastolic BP $\leq$ 90 mmHg, and if symptomatic, until symptoms resolve a .
When regorafenib is restarted, continue at the same dose level
If BP is not controlled with the addition of new or more intensive therapy, reduce by 1 dose level b .
If Grade 3 hypertension recurs despite dose reduction and antihypertensive therapy, reduce another dose level c |

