| Grade 4               | Life-threatening consequences (e.g. malignant hypertension, transient or permanent neurologic deficit, hypertensive crisis)                                              |                                                                                                                                                                                                                             | Discontinue study treatment permanently                                                                                                                                                                                                                                                                                                                                                                                            |

a. Participants requiring a delay of 28 days will be permanently discontinued.

b. If blood pressure remains controlled for at least one full cycle, dose re-escalation is permitted at the Investigator's discretion.

c. Participants requiring > 2 dose level reductions will be permanently discontinued.

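### Table 4's grade 3 hypertension hold can be triggered by systolic pressure but is released on diastolic pressure alone, so some holds have zero length

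*Protocol*

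**What the plan says.** All of the following is in Protocol section 7.2.2 and its Table 4, which govern regorafenib dosing in Arm B.

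- **Status of the table.** The section introduces it with "The dose modification schedule for treatment-emergent hypertension during study drug dosing should be followed".
- **Grade 3 trigger.** "Systolic BP $\geq$ 160 mmHg or diastolic BP $\geq$ 100 mmHg", or a need for more than one antihypertensive or for more intensive therapy than before.
- **Grade 3 hold and release.** "Hold regorafenib until diastolic BP $\leq$ 90 mmHg, and if symptomatic, until symptoms resolve". Restart is at the same dose level.
- **Treatment aim, grade 2 and grade 3 rows.** "Treat with the aim to achieve diastolic BP $\leq$ 90 mmHg".
- **Grade 2.** Asymptomatic patients stay on regorafenib. For the others: "If symptomatic, hold regorafenib until symptoms resolve AND diastolic BP $\leq$ 90 mmHg".
- **Dose reduction at grade 3.** "If BP is not controlled with the addition of new or more intensive therapy, reduce by 1 dose level". A further level is lost if grade 3 recurs despite that.
- **Footnote a.** "Participants requiring a delay of 28 days will be permanently discontinued".
- **Footnote b.** "If blood pressure remains controlled for at least one full cycle, dose re-escalation is permitted", at the investigator's discretion.

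Elsewhere, exclusion criterion 9 (section 5.3) counts systolic above 140 mmHg or diastolic above 90 mmHg, despite optimal management, as poor control. The general rule in section 7.2 withholds treatment for grade 3–4 events until grade 0–1, but gives way where a more specific rule is set.

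**The concern.** The trigger is an either/or condition on two measurements, while the release looks at only one of them. Where systolic pressure caused the hold, the measurement that caused it plays no part in ending it. Read as written, the rule lets regorafenib restart at full dose while pressure is still in the range that required stopping.

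This is not a remote event for this drug. Section 2 lists hypertension first among the common grade 3 or higher regorafenib events in the earlier phase 3 trial, at 23%. Scheduled monitoring is also thin later on. Weekly readings end with cycle 2 (section 8.1, Arm B, footnote m). From cycle 4 the only scheduled reading is on day 1 of each 56-day cycle, after the 7-day regorafenib washout.

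**Working it through.** No sample size, power or error rate is involved. The check treats trigger and release as logical conditions and applies them to example readings.

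**Inputs (Table 4).**
- Trigger on pressure: systolic ≥160 or diastolic ≥100.
- Release, asymptomatic patient: diastolic ≤90.

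| Reading | Trigger met | Release met on the same reading | Release with systolic ≤140 added |
|---|---|---|---|
| 160/90 | yes | yes | no |
| 170/85 | yes | yes | no |
| 172/84 | yes (172 ≥ 160) | yes (84 ≤ 90) | no |
| 180/80 | yes | yes | no |
| 165/95 | yes | no | no |
| 150/102 | yes | no | no |
| 165/102 | yes | no | no |

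**Case 1, isolated systolic elevation.** The first four readings meet trigger and release together, so the hold lasts 0 days. The same happens when grade 3 is reached only through a need for more intensive therapy and diastolic is already ≤90.

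**Case 2, both components raised.** A patient held at 165/95 whose diastolic falls to 90 meets release (90 ≤ 90), with systolic still grade 3 (165 ≥ 160).

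**Where the defect does not arise.** Diastolic ≥100 and diastolic ≤90 cannot hold together, so a diastolic trigger never gives immediate release. A symptomatic patient stays held until symptoms resolve.

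**Size of the gap.** Against the systolic limit of 140 in exclusion criterion 9:
- smallest possible: 160 − 140 = 20 mmHg
- 165/90: 165 − 140 = 25 mmHg
- 172/84: 172 − 140 = 32 mmHg

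Against 159, the highest systolic at which Table 4 lets an asymptomatic patient continue, the same three are 1, 6 and 13 mmHg.

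**Which rule governs.** The general grade 0–1 rule in section 7.2 would require a longer hold, but it yields to specific rules, and Table 4 is the specific rule for hypertension.

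**Comparison with the other Arm B rules.** Table 3 releases skin toxicity at grade 0–1. Table 5 releases transaminase elevations on transaminases. The non-haematologic row of Table 6 releases at grade ≤1. Each uses the measure that set the hold.

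**The case against.** The missing systolic term is not in dispute. The best arguments are that its effect is limited and that the diastolic measure was chosen.

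1. *The dose-reduction clause covers case 2.* A systolic of 165 after added therapy is, on an ordinary reading, not controlled, so the dose drops one level. This has force, and exclusion criterion 9 supports reading control on both components. But Table 4 never defines control, and its only stated target is diastolic; against that target both 172/84 and 165/90 pass. The clause also lowers the dose rather than extending the hold.
2. *140 is the wrong yardstick.* Asymptomatic patients at systolic 140–159 keep taking regorafenib, so a release at ≤140 would hold one patient at 150/85 while dosing another. The gaps on the 159 scale are indeed smaller. However, Table 4 already does this for diastolic pressure: it releases at ≤90 although asymptomatic patients at 90–99 continue. A systolic limit of 140 is the parallel value. Any limit below 160 removes the zero-length hold, so the exact figure is a clinical choice.
3. *Table 4 is not the only rule of this kind.* The haematologic row of Table 6 releases on neutrophils and platelets, whatever the haematologic event. This is right for events other than those two, and the comparison should not be pressed that far.
4. *Diastolic control was intended, and clinicians will use judgement.* The consistent use of diastolic suggests a deliberate target. Yet the protocol grades on systolic pressure and excludes on it, and gives no reason to drop it at restart. Table 3 expressly allows more conservative management; Table 4 has no such note. The duty in section 7.2.2 to control hypertension effectively concerns antihypertensive treatment.
5. *The Study Manual may supply a systolic aim.* Section 8.2.2 refers antihypertensive recommendations there, and it is not available. It could fill the gap in the treatment aim, but the hold and release rule is fixed in Table 4.

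**Conclusion.** The concern holds. As written, Table 4 gives a zero-length hold to an asymptomatic patient whose grade 3 hypertension is systolic with diastolic ≤90, and allows restart at a systolic pressure still in the grade 3 range when both components were raised. The restart is at least 20 mmHg above the entry limit of 140, or at least 1 mmHg above the highest systolic at which asymptomatic dosing continues.

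How many patients this touches cannot be stated. The 23% rate comes from patients who had failed at least two lines of therapy, and no split by systolic and diastolic trigger is given. The conclusion assumes that sites follow the table literally; antihypertensives must still be started or increased, and a site that reads control on both components would reduce the dose in some of these cases. Nothing here affects the sample size or the primary analysis. It should be fixed because it is a safety rule that gives the wrong result as written and is cheap to correct.

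**What to change.** Add a systolic condition in three places in Table 4: the grade 3 release, the symptomatic grade 2 release, and the treatment aim in both rows. For grade 3, for example: *withhold regorafenib until systolic is at most 140 mmHg and diastolic at most 90 mmHg, and until any symptoms have gone.* These limits match exclusion criterion 9; the sponsor's clinicians should set the final values. Define *controlled* by the same limits in the grade 3 dose-reduction sentence and in footnote b, and bring the Study Manual recommendations into line.

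The cost is a wording change to the grade 2 and 3 cells and footnote b at the next amendment. No assessment is added, because systolic pressure is already measured. The downside is that some holds will last longer, and a few could reach the 28-day discontinuation limit in footnote a.

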# ALT GIST

## 7.2.3. Treatment Related Hepatic Toxicity

For participants with observed worsening of serum liver tests considered related to study drug (i.e. where no alternative cause is evident, such as post-hepatic cholestasis or disease progression), the dose modification and monitoring recommendations in the below table should be followed.

Regorafenib is a UGT1A1 inhibitor. Mild, indirect (unconjugated) hyperbilirubinemia may occur in participants with Gilbert's syndrome.

Table 5:

| Observed Elevations                                                               | 1st Occurrence                                                                                                                                                                                                                                  | Restart                                                                                                                                                                                    | Recurrence  |
|-----------------------------------------------------------------------------------|-------------------------------------------------------------------------------------------------------------------------------------------------------------------------------------------------------------------------------------------------|--------------------------------------------------------------------------------------------------------------------------------------------------------------------------------------------|-------------|
| AST and/or ALT $\leq$ 5x ULN ( $<$ G3)                                            | Continue dosing, with weekly monitoring of liver function until transaminases return to $<$ 3x ULN ( $\leq$ G1) or baseline.                                                                                                                    |                                                                                                                                                                                            |             |
| ALT and/or AST $>$ 5x ULN ( $\geq$ G3)                                            | Interrupt dosing, with weekly monitoring until transaminases return to $<$ 3x ULN or baseline.                                                                                                                                                  | If the potential benefit for reinitiating regorafenib is considered to outweigh the risk of hepatotoxicity: Reduce 1 dose level and measure serum liver tests weekly for at least 4 weeks. | Discontinue |
| ALT and/or AST $>$ 20x ULN ( $\geq$ G4)                                           | Discontinue                                                                                                                                                                                                                                     |                                                                                                                                                                                            |             |
| ALT and/or AST $>$ 3X ULN ( $\geq$ Grade 2) with concurrent bilirubin $>$ 2 X ULN | Discontinue treatment and measure serum liver tests weekly until resolution. Exception: Patients with Gilbert's syndrome who develop elevated transaminases should be managed as per the recommendations outlined above for ALT/AST elevations. |                                                                                                                                                                                            |             |

NOTE: ALT, AST, and bilirubin must be obtained at baseline and monitored weekly for the first 2 cycles even if values are normal. The investigators may use investigational site or local laboratory AST, ALT, and bilirubin values for subject treatment decisions for day 8, 15 and 22 of regorafenib treatment for Cycles 1 and 2

ALT = alanine aminotransferase, AST = aspartate aminotransferase, NCI-CTCAE v 4.03 = National

Cancer Institute-Common Terminology Criteria for Adverse Events version 4.03, ULN = upper limit of normal.

In **Arm B**, for all other events related to either imatinib or regorafenib (excluding skin toxicity, treatment emergent hypertension, and hepatic dysfunction), see table below:

(Table on next page).

# ALT GIST

Table 6:

| Toxicity                         | Grade 1                          | Grade 2                         | Grade 3                                                                                                                                                                                                                                                                                                                      | Grade 4                                                                                                                                                                                  |
|----------------------------------|----------------------------------|---------------------------------|------------------------------------------------------------------------------------------------------------------------------------------------------------------------------------------------------------------------------------------------------------------------------------------------------------------------------|------------------------------------------------------------------------------------------------------------------------------------------------------------------------------------------|
| Non-haematologic                 | Continue at the same dose level  | Continue at the same dose level | Withhold dose until toxicity is grade $\leq 1$ , then resume at same dose level. If event recurs, withhold dose until toxicity is grade $\leq 1$ and reduce dose for next cycle by 1 level. Dose reduce by 1 further level for further grade 3 or higher toxicity.                                                           | Withhold dose until toxicity is grade $\leq 1$ , then reduce dose for next cycle by 1 level. Dose reduce by 1 further level for further grade 3 or higher toxicity.                      |
| Haematologic (excluding anaemia) | Continue at the same dose level. | Continue at the same dose level | Withhold dose until neutrophils $\geq 1.0$ and platelets $\geq 100$ , then resume treatment at the same dose level. If event recurs, withhold dose until neutrophils $\geq 1.0$ and platelets $\geq 100$ , and reduce dose for next cycle by 1 level. Dose reduce by 1 further level for further grade 3 or higher toxicity. | Withhold dose until neutrophils $\geq 1.0$ and platelets $\geq 100$ , then reduce dose for next cycle by 1 level. Dose reduce by 1 further level for further grade 3 or higher toxicity. |

## 7.3. Concomitant Medications/Treatments

All therapies which are considered necessary for the participant's welfare, and which are not expected to interfere with the evaluation of the study drug, may be given at the discretion of the treating clinician.

### 7.3.1. Recommended

The following medications and treatments are recommended in this study for the prevention and treatment of skin rash including hand-foot skin reaction in those on the alternating arm (Arm B):

Before initiating treatment:

- Check condition of hands and feet

During treatment:

- Avoid pressure points and protect tender areas by use of cushion inserts and well-padded footwear
- Avoid items that rub, pinch, or create friction

# ALT GIST

- Foot soaks with tepid water and Epsom salts
- Suggest a manicure/pedicure, when indicated
- Recommend pumice stone use for callus or 'rough spot' removal
- Use socks/gloves to cover moisturising creams once applied

Use of creams:

- Apply non-urea based skin-hydrating creams liberally.
- Keratolytic creams: Use sparingly and only to affected (hyperkeratotic) areas.
- Urea-based creams, Salicylic acid 6%, Alpha hydroxy acid (AHA) based creams: Concentrations of approximately 5-8% provide gentle chemical exfoliation. Apply liberally two times each day.
- Topical analgesics like lidocaine 2% should be considered for pain control.
- Topical corticosteroids should be considered for participants with grade 2 or 3 hand-foot skin reaction.

## **7.3.2. Permitted**

The following medications and treatments are permitted in this study:

- Corticosteroids
- Other palliative treatments, such as non-emergency surgery provided the circumstances of which have previously been discussed with the Study Chair (or Delegate).
- Other concomitant therapies considered necessary for the participant's well being may be prescribed at the Investigator's discretion including antiemetics, antidiarrhoeals, anti-inflammatory agents, and analgesics.
- Treatment with non-conventional therapies (for example herbs or acupuncture) and vitamin/mineral supplements is acceptable provided that they do not interfere with the study endpoints in the opinion of the Investigator.
- Bisphosphonates
- Prophylactic or therapeutic treatment with heparin as required.

## **7.3.3. Use with caution**

Pharmacokinetic data from a clinical probe substrate study indicated that regorafenib may be given concomitantly with substrates of CYP2C19 (e.g. omeprazole), CYP2C8 (e.g. rosiglitazone), CYP2C9 (e.g. S-warfarin) without a clinically meaningful drug interaction. Specific caution should be employed when considering or administering a concomitant medication that is metabolized by the phase II glucuronosyl transferases UGT1A1 and 1A9. Studies have shown regorafenib may increase systemic exposure to UGT1A1 and 1A9 substrates.

Co-administration of regorafenib may increase the plasma concentrations of BCRP substrates (e.g., methotrexate, rosuvastatin, fluvastatin, atorvastatin). Therefore, it is recommended to monitor patients closely for signs and symptoms of increased exposure to BCRP substrates

A list of CYP substrates, inhibitors, and inducers is provided at the following website: <http://medicine.iupui.edu/clinpharm/ddis/>.

- Participants taking narrow therapeutic index medications (e.g.: quinidine, cyclosporine,) should be monitored proactively.
- Co-administration of regorafenib with digoxin has no effect on plasma digoxin.

# ALT GIST

## 7.3.4. Prohibited

The following medications should **not** be used during this study:

- Systemic anticancer therapy including cytotoxic therapy, signal transduction inhibitors (including tyrosine kinase inhibitors), immunotherapy, hormonal therapy for cancer, and experimental or unapproved therapies
- Bone marrow transplant or stem cell rescue
- Use of biological response modifiers, such as granulocyte colony stimulating factor (G-CSF), within 3 weeks prior to randomisation. Note: G-CSF may be used during the study in the management of acute toxicity such as febrile neutropenia when clinically indicated or at the discretion of the Investigator; however, they may not be substituted for a required dose reduction. Routine use of G-CSF is not encouraged.
- Radiotherapy
- All traditional/alternative medicines with an anti-cancer indication, including Traditional Chinese Medicine (TCM).
- Strong cytochrome P (CYP) CYP3A4 inhibitors (eg clarithromycin, indinavir, itraconazole, ketoconazole, nefazodone, nelfinavir, posaconazole, ritonavir, saquinovir, telithromycin, voriconazole) or strong CYP3A4 inducers (eg carbamazepine, phenobarbitol, phenytoin, rifampicin, St John's wort). Co-administration of strong CYP3A4 inhibitors may lead to increased toxicity of regorafenib.
- Grapefruit juice

Subjects who require treatment with any of these agents will need to discontinue study treatment, this should be discussed with the Study Chair prior to use.

## 7.3.5. Concomitant medication reporting

Concomitant medications will not be recorded during the study, except for medications being taken at the onset of serious adverse events or medications known to interact with the study medications.

## 7.4. Treatment discontinuation

Study treatment will be permanently discontinued for any of the following reasons:

- Progressive disease (PD) is documented by a site investigator.
- Unacceptable toxicity as determined by the patient or site investigator or as defined in section 7.2.
- Delay of day 1 treatment for >28 days due to treatment-related adverse events. For delays >28 days due to reasons other than treatment-related adverse events, please contact the regional co-ordinating centre to discuss treatment continuation.
- The investigator determines that continuation of treatment is not in the patient's best interest.
- Required use of a concomitant treatment that is not permitted, as defined in section 7.3.4.
- Failure to comply with the protocol. If a patient has failed to attend scheduled assessments in the study, the clinician must attempt to determine the reason(s).
- The patient declines further study treatment.

The reasons for discontinuing treatment will be documented in the subject's medical record and eCRF.

Follow up of subjects who stop study treatment should continue according to this protocol (see section 8.1).

